#### Baseline assessments

Baseline data of participants will be recorded before the initiation of treatment: (1) Demographic information: Gender, age, height, weight, medical history, personal history, family history, study center information, and medical record number. (2) Breast cancer or malignant lymphoma information: Pathological diagnosis, staging, chest radiation therapy (side and total dose), chemotherapy regimen, and cumulative dose of anthracycline drugs. (3) Comorbidities and related medications: Including hypertension, diabetes, dyslipidemia, coronary artery disease, and other medical history.

### Statistical analysis

All statistical analyses will be performed using SPSS (version 26.0, IBM) and R (version 4.1.1). All tests will be two-sided, and a *P* value <0.05 will be considered statistically significant. The primary analysis will follow the intention-to-treat (ITT) principle, including all randomized participants and analyzing them according to their assigned groups. A per-protocol (PP) analysis will be conducted as a sensitivity analysis, and the safety analysis will include all participants who received at least one intervention. Baseline characteristics will be described by group. Continuous variables will be presented as mean ± standard deviation or median (interquartile range), depending on their distribution, while categorical variables will be expressed as frequencies and percentages. All analyses will be reported in accordance with the CONSORT Statement.

The primary outcome is the proportion of patients free from atrial arrhythmias at 3 months after intervention, which is a binary variable. It will be analyzed using a generalized linear model (GLM) with a binomial distribution and a log link function. Treatment group and study center will be included as fixed effects, and pre-specified baseline covariates—including age, sex, cancer subtype, cumulative anthracycline dose, and medical history—will be further adjusted. Results will be presented as risk ratios (RR) with corresponding 95% confidence intervals. Secondary continuous outcomes, such as AF burden, premature PAVs counts, echocardiographic parameters, and relevant biomarkers, will be analyzed using linear models (LM), with adjustment for baseline values. For repeated measures data (e.g., baseline, 3 months, and 6 months), mixed-effects models will be applied to evaluate treatment effects over time.

The incidence of adverse events and serious adverse events will be summarized as frequencies and percentages, and compared between groups using the chi-square test or Fisher's exact test, as appropriate. Changes in laboratory parameters will be described descriptively and compared between groups when necessary. Pre-specified subgroup analyses will be conducted based on cumulative anthracycline dose (e.g., high vs. low dose). Interaction terms between treatment and subgroup will be included in the model, and the Wald test will be used to assess differences in treatment effects across subgroups. The normality of model residuals will be evaluated using Q–Q plots. If the normality assumption is violated, appropriate data transformations or robust statistical methods will be applied. Missing data will be handled using multiple imputation under the assumption of missing at random, and sensitivity analyses will be performed to assess the robustness of the results. No interim analysis is planned for this study.

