
## Methods

### Study design and setting

This trial is a multicenter, double-blind, placebo-controlled study with two parallel groups designed to evaluate the efficacy of WXKL.The protocol was formulated in accordance with the SPIRIT statement and the Declaration of Helsinki (2013 Revision), as well as the Guidelines for Good Clinical Practice (GCP). The start and end of recruitment had been planned to be December 2025 and March 2028, respectively.

Before the experiment begins, researchers will conduct a training program to ensure that all participating medical staff fully understand each part of the trial. The trial will be conducted at multiple clinical centers in China, including Guang'anmen Hospital of the China Academy of Chinese Medical Sciences, Qilu Hospital of Shandong University, Xingtai People's Hospital, Affiliated Hospital of North China University of Science and Technology, Jinqiu Hospital of Liaoning Province, Tianjin Medical University Cancer Institute&Hospital, and Dezhou Second People's Hospital. After confirming eligibility and signing the informed consent form, 152 subjects receiving anthracycline treatment will be randomly allocated to either the WXKL or placebo groups in a 1:1 ratio. The study is divided into four phases: recruitment, allocation, intervention, and completion. Each participant will only be enrolled once. In addition to anthracycline chemotherapy and conventional anti-arrhythmic medications, participants will receive either WXKL or placebo treatment. During the study period, each participant will undergo three visits: baseline (Visit 1), month three (Visit 2), and month six (Visit 3). In Phase 1, participants are recruited from the oncology department, where they will undergo a physical examination and eligibility assessment. Those who match the inclusion criteria will receive a three-month pharmacological intervention. In Phase 2, following the completion of the intervention, participants will undergo clinical efficacy and safety assessments. Phase 3 is the follow-up period, during which participants will be followed up at the sixth month to gather their metrics again and assess clinical efficacy. The participant flowchart is shown in Figure 1, and the study schedule is shown in Table 1.

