### Sample size calculation

To our knowledge, this is the first clinical trial to evaluate a TCM formulation for the treatment of anthracycline-induced atrial arrhythmias. Currently, no published data are specifically available for atrial arrhythmias induced by anthracycline. Therefore, the sample size estimation was based on existing studies of TCM in the treatment of AF or PVCs, together with clinical experience and expert consensus (21–23). We assumed that the proportion of patients free from atrial arrhythmias would be 29% in the WXKL group and 10% in the placebo group. Based on a two-sided significance level of 0.05 and a statistical power of 80%, the required sample size was calculated using PASS version 15. The calculation indicated that 68 participants were needed per group. Considering an anticipated dropout rate of 10% and rounding to whole numbers, the final sample size was set at 76 participants per group, resulting in a total of 152 participants to be enrolled in this trial.

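### The fixed primary log-binomial model, with at least 12 slopes on about 27 to 30 expected successes, often has no interior solution, so the planned risk ratio and Wald interval are not secured

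*Protocol article*

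**What the plan says.** The Statistical analysis section of the protocol article fixes the primary model: "It will be analyzed using a generalized linear model (GLM) with a binomial distribution and a log link function". On its terms it says: "Treatment group and study center will be included as fixed effects". Adjustment is then added for medical history, cumulative anthracycline dose, cancer subtype, sex and age, and the result is to be a risk ratio with a 95% confidence interval. The analysis is by intention to treat on everyone randomised, with multiple imputation under missing at random. SPSS and R are the named packages.

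The Study design and setting section names seven centres. The Sample size calculation section assumes that "the proportion of patients free from atrial arrhythmias would be 29% in the WXKL group and 10% in the placebo group".

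The only remedy given for a model whose assumptions fail is transformation or robust methods, and it is triggered by non-normal residuals. It does not reach a binary log-link model.

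**The concern.** A log-binomial model sets log(p) equal to a linear predictor, so that predictor must stay at or below zero for every patient. With few successes and many terms, the likelihood is often maximised where at least one patient has a fitted probability of exactly 1. No interior maximum then exists. Standard fitting either does not converge or stops at the edge, and the curvature-based standard error no longer supports a Wald interval. A centre with no success adds a second problem, because its coefficient runs to minus infinity.

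The trial's single primary result is at stake. If the stated model cannot be fitted, someone must decide which covariates to drop, whether to merge centres, or which other model to use. The Randomization and blinding section has the statisticians analyse after a first unblinding that separates the groups, so that choice would be made with the groups already split. Multiple imputation adds to the burden, because the model has to fit in every imputed data set.

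**Working it through.** **The plan's own figure.** With p1 = 0.29, p2 = 0.10, mean 0.195, two-sided 0.05 and 80% power:

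n = [1.96 × √(2 × 0.195 × 0.805) + 0.8416 × √(0.29 × 0.71 + 0.10 × 0.90)]² / 0.19² = (1.098 + 0.458)² / 0.0361 = 67.1, rounded up to 68.

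Then 68 / 0.9 = 75.6, rounded up to 76. Both stated figures are reproduced. The sample size is not at issue.

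**Expected successes.**
- All 152 patients: 76 × (0.29 + 0.10) = 29.6.
- 136 evaluable patients: 68 × 0.39 = 26.5.

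**Number of terms.**
- Smallest reading: 1 treatment + 6 centre + 5 covariates = 12 slopes, or 13 parameters with the intercept. Successes per slope: 26.5 / 12 = 2.2 to 29.6 / 12 = 2.5.
- If medical history is coded as four indicators (hypertension, diabetes, dyslipidaemia and coronary disease, which the Baseline assessments section records): 15 slopes, 16 parameters. Successes per slope: 26.5 / 15 = 1.8 to 29.6 / 15 = 2.0.

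**Where the maximum lies.** The log-binomial likelihood is concave, so its constrained maximum can be found directly, without relying on any package's fitting routine. This was done with 300 simulated trials per scenario over 24 scenarios. The Monte Carlo standard error near 50% is √(0.25 / 300), about 3 percentage points. Modest effects means a log risk ratio of -0.2 to -0.3 per SD of age and of dose.

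| Model | Assumed covariate effects | Maximum on the boundary |
|---|---|---|
| 13 parameters | none | 40-55% |
| 13 parameters | modest | 63-83% |
| 16 parameters | none | 68-81% |
| 16 parameters | modest | 84-94% |

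**Cross-check with R's glm, valid starting values supplied.** The share of trials without a clean fit (non-convergence or a boundary solution) was:
- 43-54% with 13 parameters and no effects;
- 74-84% with 16 parameters and no effects;
- 63-93% with moderate effects, over both model sizes;
- 90-97% with stronger effects.

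The most favourable case tried had every covariate binary and without effect. It still left 43% without a clean fit.

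**Centres without a success.** With seven equal centres, the expected successes per centre are 26.5 / 7 = 3.8 to 29.6 / 7 = 4.2. A Poisson approximation to the chance of at least one empty centre gives 1 - (1 - e^-3.8)^7 = 0.15 and 1 - (1 - e^-4.2)^7 = 0.10. The glm simulation gave 7-17% with equal centres and 33-43% with assumed shares running from 30% down to 5%.

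**Alternatives on the same simulated data.** A Poisson log-link model with the same terms converged with a finite treatment risk ratio in 99-100% of trials. A log-binomial model with treatment alone fitted in every trial.

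**The case against.** Several points on the other side have force.

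- **An unseen analysis plan may hold a fallback.** Convergence rules, covariate coding and centre pooling are ordinary SAP content, and their absence from an article is no finding. That stands. The point here is narrower: the model the article commits to fits poorly with the article's own rates, sample size and centre count.
- **The model may be smaller than assumed.** With treatment and centre only, the log-binomial fit is mostly clean: 96-100% at n = 152 with starting values supplied, and 77-91% with default ones. One could read the covariates as belonging to a second, adjusted analysis. That reading is strained, because the text describes one primary model and one result. The 16-parameter count is also an assumption. The article says only medical history, and the four conditions come from a list of baseline data to be recorded.
- **Failure depends on software.** A reader might infer near-certain failure, since R's default starting values gave an outright error in 96-99% of simulated trials under one set of assumptions. That figure mainly reflects the starting values, which are routinely supplied by hand, and SPSS was not tested. The boundary rates in the table do not depend on the package.
- **Type I error.** A reader might infer an inflated error rate. Under a 10%/10% null, rejection of 9% was seen at n = 136-137 when every returned P value was accepted. At n = 152 with 13 terms it was 6-8%, and about 4% among clean fits. The plan does not say that it would accept boundary P values, and intention to treat with imputation implies n = 152.
- **Blinding.** The first unblinding splits the groups and a second one names them, so a change of model need not be made knowing which group is WXKL. This lowers the risk of a favourable choice without removing it.

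**Conclusion.** The concern holds as a weakness of a stated method. On the smallest reading of the model, and assuming that no covariate matters, the planned risk ratio with a Wald 95% interval is not validly obtainable in about 40-55% of trials. With modest covariate effects or four history indicators the figure is about 65-95%. The counts of successes and slopes follow from the article. The percentages rest on assumed covariate distributions, covariate effects and centre sizes, for which the article gives no data.

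In the most favourable scenarios the odds are roughly even, so the documents do not support saying that the model will fail in any given trial. They also do not support a claim of a fixed inflation of type I error, or a claim that centre must leave the model.

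**What to change.** Before any unblinding, replace the primary model with one that estimates the same risk ratio without the log-binomial constraint. Either of these will do:
- modified Poisson regression with a robust standard error, corrected for small samples; or
- logistic regression standardised over the trial population to a marginal risk ratio.

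Use the chosen model in every imputed data set. Fix a short covariate list and its coding in advance, with medical history as a single term, and write a rule for pooling small centres that is applied blind to treatment.

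The short list matters as much as the change of model. With all 16 terms kept, modified Poisson still showed 6-8% type I error in simulation. With treatment and three covariates, it gave 3.8-4.2% and about 82% power, and the standardised logistic model gave 2.8-3.5% and about 81%. Those results rest on assumed covariates, and the article does not say which baseline factors predict outcome, so the choice needs clinical input.

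The cost is one paragraph of protocol or SAP wording, with no extra patients or data. The price is slightly less adjustment for covariates and centre.

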#### Inclusion criteria

The inclusion criteria for this study include the following conditions: 1) Age 18–80 years; 2) Having a confirmed pathological type, receiving chemotherapy for the first time, with an expected cumulative anthracycline dose ≥200 mg/m², and PAVs or AF after at least one cycle of anthracycline therapy, with ambulatory electrocardiography showing PAVs ≥100 beats per 24 h or meeting the diagnostic criteria for AF; 3) No history of PAVs or AF; 4) No prior history of chest radiotherapy, targeted therapy, or immunotherapy; 5) Eastern Cooperative Oncology Group (ECOG) performance status < 2; 6) Willing to be randomly assigned to either the WXKL group or the control group; 7) Voluntary participation in the trial and provision of signed informed consent.

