### Outcome evaluation

#### Primary outcome

The primary endpoint is the proportion of patients in both groups free of atrial arrhythmias 3 months after intervention, defined as the absence of any single episode of AF lasting ≥30 s or PAVs ≥100 beats per 24 h as detected by 24 h Holter monitoring.

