This study also has several limitations. First, arrhythmias assessment is based on 24 h Holter monitoring. Although this method is widely used in clinical research, its relatively short monitoring duration may lead to underdetection of intermittent atrial arrhythmias; extending the monitoring period or using implantable devices may improve detection rates (35). However, in multicenter randomized controlled trials, 24 h Holter monitoring remains a practical approach due to its feasibility, high patient compliance, non-invasiveness, and relatively low cost. Moreover, it can provide standardized and reproducible quantitative metrics, such as AF episodes and PAVs burden, and is therefore still commonly used in clinical trials (36). Second, although most clinical trials currently define AF as a single episode lasting ≥30 s (37), there is no universally accepted definition for frequent PAVs (38, 39). Previous studies have used varying thresholds for PAVs; for example, some have defined it as ≥500 beats per 24 h, whereas others have used ≥ 720 beats per 24 h or ≥1,000 beats per 24 h (22, 38). Although no consensus cutoff has been established, the clinical significance of frequent PAVs is primarily reflected in the strong association between increasing PAVs burden and the risk of AF (12). Based on these considerations, in the present study design, we integrated evidence from the literature and expert opinions in the field of cardio-oncology, while taking into account the overall condition and treatment tolerance of patients undergoing chemotherapy. A relatively conservative threshold ((≥100 beats per 24 h) was adopted as the inclusion criterion. This approach may enhance the sensitivity for detecting potential anthracycline-induced atrial arrhythmias within a limited monitoring period, thereby enabling earlier identification of clinically meaningful atrial electrical abnormalities. Nevertheless, it should be acknowledged that the choice of different thresholds may influence event detection rates and the comparability of study results, which represents an inherent limitation. Further prospective studies are warranted to establish the optimal clinical cutoff for frequent PAVs in the field of cardio-oncology. Finally, due to the lack of published data specifically targeting this study population, the assumptions used for sample size estimation were derived from studies involving AF and related PAVs, combined with clinical experience and expert opinion, which may introduce uncertainty. Larger-scale trials are therefore needed to further validate the clinical benefits of WXKL.

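### The primary model names no baseline arrhythmia measure, although entry and response share the same Holter cut-off; omission costs some precision and protection against chance imbalance

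*Protocol article*

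**What the plan says.** **Entry** (Protocol article, Inclusion criteria). Patients qualify "with ambulatory electrocardiography showing PAVs" at or above 100 beats per 24 h, or by meeting the diagnostic criteria for AF. They must have no earlier history of either arrhythmia.

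**Response** (Primary outcome; Measurements). Being arrhythmia-free at month 3 is "defined as the absence of any single episode of AF lasting" at least 30 s, and fewer than 100 premature beats, on 24 h Holter. Table 1 lists one Holter item at each visit, baseline included.

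**Primary model** (Statistical analysis). This is a binomial GLM with log link, reported as a risk ratio, with treatment and centre as fixed effects. In addition, "pre-specified baseline covariates—including age, sex, cancer subtype, cumulative anthracycline dose, and medical history—will be further adjusted". The same section adjusts secondary continuous outcomes, PAC count among them, for their baseline values.

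**Allocation** (Randomization and blinding). Central, 1:1. No stratification factor is stated.

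**Sample size** (Sample size calculation). The arrhythmia-free proportion "would be 29% in the WXKL group and 10% in the placebo group"; with a "two-sided significance level of 0.05 and a statistical power of 80" percent, "68 participants were needed per group"; allowing for "an anticipated dropout rate of 10" percent, 76 per group are enrolled.

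**The concern.** One cut-off makes someone a patient and later makes the same person a responder. A patient who enters at 105 beats responds by losing 6. One who enters at 5,000 must lose just over 98%. A patient who enters with AF is judged on whether one later day is free of a 30 s episode as well as on the beat count. The Discussion accepts that with 24 h Holter "its relatively short monitoring duration may lead to underdetection of intermittent atrial arrhythmias". Unless counts on different days are nearly unrelated, the baseline value should predict the endpoint well.

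The protocol chose a covariate list for the primary model and left out the endpoint's own baseline. Medical history cannot stand in for it, because prior PACs or AF are not allowed at entry. Nor does the stated allocation balance the arms on rhythm. What is at stake is efficiency, and how far a reader can trust the single result if one arm happens to receive more near-threshold patients.

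**Working it through.** **1. The plan's own figure.** Inputs from Sample size calculation: p1 = 0.29, p2 = 0.10, two-sided alpha 0.05, power 80%. Pooled-variance formula without continuity correction, with mean proportion 0.195:

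n = [1.960·√(2·0.195·0.805) + 0.842·√(0.29·0.71 + 0.10·0.90)]² / 0.19² = (1.098 + 0.458)² / 0.0361 = 67.1, rounded up to **68**.

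Inflation for dropout: 68/0.90 = 75.6, rounded up to **76**. Both stated figures reproduce. Power by this formula is 80.5% at 68 per arm and 84.8% at 76.

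**2. Responders available to the model.** 68 × (0.29 + 0.10) = 26.5 and 76 × 0.39 = 29.6, so about 27 to 30 in total. Seven named centres give six contrasts. With treatment and at least five covariates, the model already has at least 1 + 6 + 5 = 12 terms.

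**3. How prognostic could the baseline count be?** The documents give no count distribution, so this is an illustration on assumptions: log-normal counts, SD 0.8 on log10, source-population median 100 beats, no treatment effect. Share arrhythmia-free at follow-up, by quartile of baseline count among patients entering at 100 or more:

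| Within-patient correlation | Q1 | Q2 | Q3 | Q4 |
|---|---|---|---|---|
| 0.5 | 46% | 39% | 30% | 18% |
| 0.7 | 44% | 32% | 19% | 7% |
| 0.9 | 38% | 16% | 4% | 0% |

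Only the gradient matters here; the levels are not estimates of the placebo rate.

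**4. Power gained by adjusting.** Simulation with 68 per arm and marginal rates held at 10% and 29%, using a logistic likelihood-ratio test with and without baseline log count. The odds ratio per SD of log count is assumed.

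| Odds ratio per SD | Without | With |
|---|---|---|
| 1 | 82% | 82% |
| 1.5 | 82% | 83% |
| 2 | 82% | 84% |
| 3 | 82% | 87% |
| 4 | 82% | 90% |

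The gain is 0 to 8 points (Monte Carlo standard error about 0.9 points on each power). Type I error is about 5 to 6% either way. Centre and the other covariates were left out, so this indicates size only.

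**5. Chance imbalance at 76 per arm.** The standard error of the standardised baseline difference is √(2/76) = 0.162. The 95% limit is 1.96 × 0.162 = 0.32 SD, and P(|difference| > 0.2 SD) = 22%. With no drug effect and a 10% base rate, a 0.32 SD imbalance alone produces:

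| Odds ratio per SD | Rates in the two arms | Apparent RR |
|---|---|---|
| 1.5 | 10.6% vs 9.4% | 1.12 |
| 2 | 11.0% vs 9.1% | 1.21 |
| 3 | 11.5% vs 8.7% | 1.32 |

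For rhythm, if a share q qualifies by AF, the 95% limit on the difference between arms is 1.96·√(2q(1−q)/76). That is 10 points at q = 0.10 and 15 points at q = 0.30 (q is assumed).

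**6. Does the planned model tolerate the covariate?** Log-binomial fits by ordinary iteratively reweighted least squares were tried on simulated trials of 152 patients (10% vs 29%, outcomes generated from a logistic model). Treatment alone always gave a usable fit. Adding one continuous covariate gave a usable fit in roughly 55%, 18% and 8% of trials at odds ratios per SD of 2, 3 and 4. A constrained algorithm would do better, but the more useful the covariate, the worse this link behaves.

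**The case against.** The best counter-argument is that this is a matter of efficiency, not validity. In a randomised trial, leaving out a prognostic covariate neither biases the treatment comparison on average nor raises type I error, and the confidence interval already allows for chance imbalance. That stands. The sample size was also set without covariates, and it reproduces.

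Second, the covariate list is introduced as non-exhaustive, and a SAP that is not shown could add the baseline measures. This stands in part. But the protocol did commit to naming covariates for the primary model, and it named less direct ones. It also applied baseline adjustment to the secondary continuous outcomes. An open list for a primary model is itself a reason to close it before unblinding.

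Third, every size above rests on inputs that the documents do not supply: count distribution, day-to-day variation and AF share. That stands, so the gain is given as a range that starts at zero. The likely strength of the baseline count is inferred from how the endpoint is built, not from data.

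Fourth, adding a strong continuous covariate to a log-binomial model with about 30 responders may break it. That stands, so the fix needs a fallback and should replace terms instead of adding them. Dropping centre would be a matter of preference and is not asked for.

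**Conclusion.** The point holds as an improvement to the primary analysis. Entry and response share one definition, the closest predictors of response are measured at Visit 1, and neither the named covariates nor the stated allocation uses them. The cost is about 0 to 8 points of power, negligible if the baseline count predicts weakly. There is also exposure in the one realised trial to an imbalance that, at its 95% limit, could by itself produce an apparent RR of about 1.1 to 1.3. Both ranges depend on the assumed odds ratio per SD.

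A reader might infer more, in three ways that the documents do not support:

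- **That the primary test is biased or its type I error inflated.** It is not, as the simulation in the working shows.
- **That the 10% placebo rate overlooks patients who fall below 100 beats by regression to the mean.** The rate is attributed to earlier studies, clinical experience and expert consensus. Whether these already reflect such patients cannot be known from the article.
- **That the trial is underpowered if more placebo patients respond.** Power at 68 per arm falls to 69%, 62% and 60% at placebo rates of 20%, 30% and 40% only if the gain stays at 19 percentage points. At the odds ratio implied by the assumed rates, (0.29/0.71)/(0.10/0.90) = 3.7, it is 94 to 96%. The protocol fixes neither scale for other placebo rates, and its planned effect measure is the risk ratio.

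The stated 68 and 76 per arm are correct for the stated assumptions.

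**What to change.** Before unblinding, in the protocol or the SAP:

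1. Name log baseline PAC count and qualifying arrhythmia (AF versus PAC only) as covariates in the primary model. State how zero counts are handled, for example log(count + 1).
2. Let them replace weaker terms, such as the unspecified medical history item, so that the model does not grow against 27 to 30 expected responders. Close the list.
3. Pre-specify what is reported if the log-binomial model does not converge. Examples are modified Poisson regression with robust standard errors, or a risk ratio standardised from logistic regression. Both keep the RR as the effect measure.

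**Cost.** No new data and no change in sample size, since the 24 h Holter is already scheduled at baseline. The downside is small: one weaker covariate is lost and the fallback needs a few lines of text.

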## Discussion

Anthracycline-induced cardiotoxicity remains a challenging clinical issue in cancer treatment. Despite the unshakable role of these agents in treating breast cancer, lymphoma, and other malignancies, their associated cardiac injury—particularly early-onset atrial arrhythmias—significantly impacts treatment tolerance and long-term patient outcomes (27). Effective management of this complication is not only a vital mission for cardio-oncology but also an essential requirement for achieving comprehensive, high-quality survival for cancer patients (28). Previously, clinical management strategies for such arrhythmias primarily relied on conventional anti-arrhythmic drugs, but their application in the specialized population of cancer patients often presents challenges. Moreover, patients frequently exhibit reduced tolerance to standard pharmacotherapy due to metabolic disturbances from the cancer or its treatment, increased multi-organ burden, and complex drug interactions. Furthermore, the potential negative inotropic effects or arrhythmogenic risks associated with certain drugs raise concerns about the safety of their long-term use.

As an important alternative and complementary therapy, WXKL demonstrate significant potential and clinical value in preventing and treating such complications due to their multi-component, multi-target, and holistic regulatory properties (29, 30). Extensive prior research indicates that this medication exerts its anti-arrhythmic effects through multiple mechanisms, including anti-oxidant stress, energy metabolism regulation, anti-inflammatory and anti-apoptotic actions, and modulation of sodium-calcium channels (31–34). This provides theoretical support for its application in treating anthracycline-induced atrial arrhythmias. However, in clinical practice to date, no randomized controlled trials have specifically investigated the efficacy and safety of WXKL in anthracycline-induced atrial arrhythmias. To address this evidence gap, the research team designed this multicenter, randomized, double-blind, placebo-controlled trial. It aims to overcome limitations of previous studies, generate high-level evidence for WXKL in cardio-oncology, specifically for anthracycline-induced atrial arrhythmias, and to further validate its efficacy and safety.

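### The only between-arm analysis named for adverse events is a significance test, which cannot show how much excess harm remains possible in a trial sized on efficacy

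*Protocol article*

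**What the plan says.** The Abstract gives the aim as evaluating both efficacy and safety. The Discussion uses a stronger verb: the trial is "to further validate its efficacy and safety".

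The Statistical analysis section fixes the AE analysis in one sentence. "The incidence of adverse events and serious adverse events will be summarized as frequencies and percentages", and these are then "compared between groups using the chi-square test or Fisher's exact test, as appropriate". The same section sets a rule for every test: "All tests will be two-sided, and a *P* value <0.05 will be considered statistically significant". A risk ratio with a 95% confidence interval is specified for the primary outcome. No estimate, interval or margin is named for AEs or SAEs. Laboratory changes are described, and compared between groups when necessary.

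The Sample size calculation section rests on efficacy alone, assuming that "the proportion of patients free from atrial arrhythmias would be 29% in the WXKL group and 10% in the placebo group". That gives 68 per arm, and 76 after allowing for 10% dropout.

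Two other safeguards are described. The Safety evaluation section provides for detailed AE recording and a review of relatedness. The Data security monitoring and management section sets up an independent Data Monitoring Committee (DMC) that reviews AEs across groups.

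**The concern.** A test of no difference answers whether an excess of events is larger than chance would readily produce. A statement about safety needs a different answer: how large an excess the data still allow. In a trial of this size the two can diverge widely for uncommon events, which include many individual AEs and SAEs. A sizeable excess can give a non-significant result, and the P value does not show the reader how much harm has been left open.

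At stake is the quality of the safety statement for a product given alongside anthracycline chemotherapy and, in some patients, β-blockers. The primary efficacy analysis is not affected.

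**Working it through.** **Inputs from the protocol article.** 29% vs 10% for the primary outcome, two-sided alpha 0.05, power 80%, 68 per arm, 10% dropout, 76 per arm (Sample size calculation); chi-square or Fisher's exact test at two-sided 0.05 for AEs and SAEs (Statistical analysis). The safety population is everyone who received at least one intervention, so at most 76 per arm.

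**Assumed.** All AE rates, because the article gives none.

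**Step 1: reproduce the plan's own figure.** With pooled variance and p̄ = (0.29 + 0.10)/2 = 0.195,

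n = [1.960 × √(2 × 0.195 × 0.805) + 0.842 × √(0.29 × 0.71 + 0.10 × 0.90)]² / 0.19² = (1.960 × 0.5603 + 0.842 × 0.5440)² / 0.0361 ≈ 67.1, so 68.

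Dropout: 68 / 0.90 = 75.6, so 76. Both stated figures reproduce. The calculation contains no safety input.

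**Step 2: power of the named tests for a doubling, 76 per arm.** For each pair of counts (a, b), take the product of the two binomial probabilities. Sum it over all pairs where the test gives two-sided P < 0.05. The chi-square is the uncorrected Pearson test.

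| Control → WXKL | Power, chi-square | Power, Fisher | Missed |
|---|---|---|---|
| 2% → 4% | 0.095 | 0.022 | 90–98% |
| 5% → 10% | 0.220 | 0.131 | 78–87% |
| 10% → 20% | 0.416 | 0.328 | 58–67% |
| 15% → 30% | 0.608 | 0.535 | 39–46% |
| 20% → 40% | 0.775 | 0.722 | 22–28% |
| 25% → 50% | 0.902 | 0.870 | 10–13% |

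Power crosses 50% at a control rate of about 12% for chi-square (0.497 at 12%) and about 14% for Fisher (0.493 at 14%). With 68 per arm, power for 10% vs 20% falls to 0.370 and 0.293.

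**Step 3: what a P value leaves unsaid.** Take 10/76 on WXKL and 4/76 on placebo, which is 13.2% vs 5.3%, a risk ratio of 2.5.

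- Chi-square: pooled rate 14/152 = 0.0921; z = 0.0789 / √(0.0921 × 0.9079 × 2/76) = 0.0789 / 0.0469 = 1.68; P = 0.09. Fisher: P = 0.16.
- Newcombe 95% CI: the Wilson limits are 0.073 to 0.226 for 10/76 and 0.021 to 0.128 for 4/76.
 - Lower: 0.0789 − √[(0.1316 − 0.0731)² + (0.1277 − 0.0526)²] = −0.016.
 - Upper: 0.0789 + √[(0.2255 − 0.1316)² + (0.0526 − 0.0207)²] = 0.178.

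The test reports no significant difference. The interval says that an excess of up to about 18 percentage points has not been excluded.

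**Step 4: equal counts.** The upper 95% limit for the risk ratio is exp[1.96 × √(2/k − 2/76)] for k events in each arm. It is 3.9 for 4 vs 4 and 2.5 for 8 vs 8, so even identical observed rates do not exclude a doubling at these frequencies.

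**The case against.** A reader might infer that the plan will take P > 0.05 as proof of safety, or that the tests are the means by which safety is to be validated. The documents support neither. No sentence says how a non-significant AE result will be read. The verb *validate* stands in the Discussion, which does not mention the tests, and the Statistical analysis section does not speak of validation.

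A reader might also infer that a doubling is usually missed at any rate. That is wrong: at control rates of 20% or more the tests detect a doubling at least 72% of the time, and overall AE incidence during chemotherapy could lie in that range.

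Four further points deserve weight.

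- Safety does not rest on one test. Relatedness review, laboratory data and the DMC all contribute. This stands, but none of them is specified to give a between-arm estimate of excess AE risk.
- Counts and percentages by arm will be reported, so anyone could compute the interval. True, but the planned comparison remains the test.
- Under the usual expected-count convention, chi-square would apply at 10% vs 20% (about 11 expected events per arm), so the Fisher end of that range is less relevant. This stands. The chi-square figure alone is still 58% missed.
- Sizing on the primary outcome and testing AEs descriptively are common, and an unseen analysis plan may add intervals. Sizing on efficacy is indeed no error. But the article does not leave the AE comparison open: it names a method, and that method does not fit a safety aim.

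**Conclusion.** The point holds in a limited form. The article names a significance test as its between-arm analysis of AEs and SAEs, and such a test cannot bound excess harm in a trial sized on efficacy. For events with a control rate below about 12% (chi-square) or 14% (Fisher), a true doubling would be missed more than half the time with 76 per arm. For common events the tests detect a doubling reasonably well.

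These figures assume 76 per arm in the safety population, independent binomial counts and AE rates that are not in the article. The argument for an interval does not depend on those rates. The change should be made, but it concerns the reporting and interpretation of safety only.

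**What to change.** In the Statistical analysis section, make the between-arm risk difference with its 95% CI (for example Newcombe) the main safety comparison for any AE, SAEs and treatment-related AEs. Keep the chi-square or Fisher P values only if they are labelled descriptive. State that the safety conclusion will quote the upper confidence limit, that is, the excess risk not excluded. In the Discussion, replace *validate* with *evaluate* for safety, in line with the Abstract.

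The cost is some wording and a few table columns from data already collected, with no extra patients or procedures. The small downside is a less favourable safety claim, because the intervals will be wide.
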